### Sample size calculation

Our sample size calculation is based on the conventional significance (alpha) and power (1-beta) levels of 0.05 and 0.80 respectively, planning one-sided testing. We assume a baseline incidence rate of mood and anxiety disorders of 0.11/person*year for the control condition, based on our own unpublished analyses in high risk offspring from the ARIADNE study; in the ultra-high risk subgroup of children with 2 or 3 risk factors we found a 10-year cumulative incidence of anxiety- and mood-disorders of 0.67 (time frame: age 10–20), which corresponds to an incidence rate of 0.11/person*year, assuming a constant rate. With an intended follow-up duration of 2 years, we would then need a minimum of 81 participants per condition to give our study sufficient power to detect a clinically meaningful effect of the intervention on the time to onset of episodes of mood- and anxiety disorders. We compared our estimated incidence rates with two prevention studies. Clarke et al. [13], who studied the effect of a preventive program in subsyndromal offspring of depressed patients, found a 1 year cumulative incidence of 0.25 for depression alone (rate 0.29/person*year). Therefore, our incidence assumption is relatively conservative. We assume a risk reduction of 70% for the treatment condition, based on the Clarke study; the 1 year cumulative incidence of depression in the intervention group is 0.08, compared to 0.25 in the control group (unadjusted hazard ratio 0.29). The reported adjusted hazard ratio in this study is 0.18. Dadds et al. [67] report a hazard ratio of 0.22 in favor of a program aimed at preventing anxiety disorders in children. Again, we choose the more conservative estimate. Nevertheless, realizing that above-mentioned assumptions remain uncertain and that participants may drop out, we decided to include another 25%, resulting in 2 groups of 102 children for the intervention phase (N = 204).

Including 554 children for the screening (T0), we estimate that 388 children will be in the ultra high risk group (70%) and 166 children in the no ultra high risk group (30%). We anticipate 20% of the eligible children to already suffer from a mental disorder that warrants treatment, and another 20% to not want to participate in the intervention phase of the study for various reasons (leaving N = 204 for randomization). In order to include 554 children in the screening, we anticipate that we need to select 2770 adult patient files (80% no children in the right age range or no interest in participating in the study). This percentage was based on our earlier experience with the epidemiological ARIADNE study, following offspring over time.

### Statistical analyses

Survival analysis will be used to answer the first research question (effect of treatment on the possible onset of depression or anxiety disorder). It encompasses a wide variety of methods for analyzing the timing of events. The logrank test (sometimes called the Mantel-Cox test) is a hypothesis test and will be used to compare the ‘survival’ distribution between the intervention and the control group. The measurement is the time to event (clinical onset of anxiety disorder or depression). Therefore ‘survival’ is ‘no onset of an anxiety or mood disorder’ in the study period of 2 years.

All data will be analyzed using the intent-to-treat principle. Multilevel analysis is a general term referring to statistical methods appropriate for the analysis of data sets comprising several types of units of analysis. Multilevel analysis holds two important features that are relevant to our data, namely the handling of missing data, as well as the possibility to work with dependent data. In our case, siblings are dependent (“nested”) data and can be analyzed as such. Intention to treat analyses are done to avoid the effects of crossover and drop-out, which may break the randomization to the treatment groups in the study. Mediators and moderators can be included as explanatory variables into the multilevel model.

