#### Randomisation

Since outcome may be dependent on treatment centre and the pathway of inclusion (through elevated symptoms versus no symptoms/HRI only), we decided to work with stratified allocation to treatment condition to ensure a balanced number of participants over conditions. A web-based computer program allows for dynamic on-the-spot randomisation. Randomisation is based on the defined strata as well as on the assigned treatment condition of earlier subjects within the strata. To prevent conscious or unconscious influence on the recruiting team, we choose to conceal the exact details of the randomisation process at this stage (following the recommendations of the CONSORT guidelines [39]). Randomisation takes place after the whole assessment has been completed, so that the first assessment is not dependent on the participant’s knowledge of treatment condition. The research assistant assigns a unique code to each participant. In case one family has several high risk children, the youngest child is entered for randomisation, and the siblings are assigned to the same condition. The research assistant then enters the number of the participant in the web-based randomisation program, and at that moment the computer randomly assigns the treatment condition (active intervention or minimal information; 1:1).

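### The primary log-rank test, as stated, does not carry the two randomisation strata (centre and inclusion pathway); the loss is small, and one sentence would repair it

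*Protocol article*

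**What the plan says.** The Randomisation section gives a prognostic reason for stratifying: "Since outcome may be dependent on treatment centre and the pathway of inclusion", where pathway means elevated symptoms versus High Risk Index only. It continues: "we decided to work with stratified allocation to treatment condition to ensure a balanced number of participants over conditions". Allocation is dynamic within strata and 1:1. When a family has several high-risk children, the youngest is randomised and the siblings receive the same condition.

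The Statistical analyses section fixes the primary test: "The logrank test (sometimes called the Mantel-Cox test) is a hypothesis test and will be used to compare the" survival distributions of intervention and control. Strata and covariates are not mentioned. Its multilevel text covers missing data, sibling dependence, mediators and moderators. Centre and pathway appear nowhere in the section, and the sibling remark is attached to the multilevel model, not to the log-rank test.

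The Sample size calculation section plans on "conventional significance (alpha) and power (1-beta) levels of 0.05 and 0.80 respectively, planning one-sided testing", a control rate of 0.11 per person-year, a 70% reduction, 2 years of follow-up and 81 children per arm, raised to 102. The Ethical approval section lists three sites.

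**The concern.** When balance is forced on factors that predict outcome, the arms differ less by chance than the unstratified log-rank variance supposes. The test statistic then has a null standard deviation below 1, so the test rejects less often than its nominal level and gives up some power. The design pays for the stratification and the stated analysis does not collect the benefit.

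The sibling rule adds two complications. A sibling may have entered by a different pathway from the youngest child, so pathway balance is not guaranteed at child level. Siblings in the same arm also have correlated outcomes, which a plain log-rank test treats as independent.

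At stake is a modest amount of precision in a trial planned on few events. Leaving the form of the test open also leaves a later choice between stratified and unstratified results.

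**Working it through.** **Reproducing the plan's figure.** Inputs from Sample size calculation: "We assume a baseline incidence rate of mood and anxiety disorders of 0.11/person*year for the control condition"; "We assume a risk reduction of 70% for the treatment condition", taken as a hazard ratio of 0.30; one-sided 0.05; power 0.80; 2 years.

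- Control 2-year risk: 1 − exp(−0.11 × 2) = 0.197.
- Intervention 2-year risk: 1 − exp(−0.11 × 2 × 0.30) = 0.064. The mean is 0.131.
- Freedman events, unstratified log-rank: (1.645 + 0.842)² × (1.30/0.70)² = 21.3.
- Per arm: 21.3 / (2 × 0.131) = 81.6 before rounding of the inputs. The plan says 81, so the figure reproduces.
- Expected events: 162 × 0.1307 = 21.2 with 81 per arm, and 204 × 0.1307 = 26.7 with 102 per arm and no dropout.

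**Simulation of the two tests on the same data.** Six strata of equal expected size (3 sites × 2 pathways, an assumption), blocks of four within strata, mean control rate 0.11, exponential onset and 2 years. There were 8,000 runs under the null and 4,000 for power. The document gives no rates by centre and none by pathway within one cohort, so stratum strength is varied. The pathway ratio of 2.6 is 0.29/0.11, two rates quoted in Sample size calculation. The centre factor is the ratio between adjacent centres. Each cell is unstratified / stratified.

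| Setting | Pathway ratio, centre factor | One-sided alpha | Null SD of Z | Power, HR 0.30 | Power, HR 0.50 |
|---|---|---|---|---|---|
| 162, no dropout | 1, 1 | 0.045 / 0.045 | 0.995 / 0.995 | 0.831 / 0.830 | 0.515 / 0.513 |
| 162, no dropout | 2.6, 1 | 0.047 / 0.049 | 0.967 / 0.984 | 0.827 / 0.832 | 0.492 / 0.498 |
| 162, no dropout | 2.6, 1.5 | 0.048 / 0.054 | 0.986 / 1.015 | 0.818 / 0.828 | 0.495 / 0.508 |
| 162, no dropout | 5, 2 | 0.036 / 0.050 | 0.919 / 0.995 | 0.787 / 0.816 | 0.437 / 0.483 |
| 204, 25% dropout | 1, 1 | 0.050 / 0.051 | 0.996 / 0.997 | 0.867 / 0.863 | 0.545 / 0.539 |
| 204, 25% dropout | 2.6, 1 | 0.044 / 0.047 | 0.975 / 0.993 | 0.844 / 0.844 | 0.539 / 0.549 |
| 204, 25% dropout | 2.6, 1.5 | 0.047 / 0.052 | 0.971 / 0.998 | 0.846 / 0.857 | 0.519 / 0.532 |
| 204, 25% dropout | 5, 2 | 0.039 / 0.048 | 0.932 / 0.999 | 0.819 / 0.846 | 0.485 / 0.515 |

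The Monte Carlo standard error is about 0.0024 for alpha and 0.006 to 0.008 for each power figure.

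- **2.6-fold pathways:** unstratified alpha is 0.044 to 0.048 in the table, or about 0.043 to 0.048 allowing for simulation error. Power loss is 0 to 1 point at HR 0.30 and 0.6 to 1.4 points at HR 0.50.
- **Very strong strata (5-fold pathways, 2-fold centres):** alpha is 0.036 to 0.039. Power loss is about 3 points at HR 0.30, and 3.0 and 4.6 points at HR 0.50.
- **No prognostic strata:** stratifying costs at most 0.6 point.

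A separate 6,000-run check used 204 children, strata at 0.11 and 0.29, and exact balance. It gave alpha 0.040 / 0.048 and, at HR 0.50, power 76.5% / 77.8%. That setting produces about 51 events, roughly twice the planned number, so it confirms the direction but does not describe the planned trial.

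**Siblings.** The simulation has no siblings. With a 2.6-fold pathway ratio the null variance of Z is 0.967² = 0.935 to 0.986² = 0.972. A sibling variance inflation of 1/0.972 = 1.03 to 1/0.935 = 1.07 would therefore cancel the conservatism. As an illustration, one earlier family trial described in the Background had 155 children in 111 families, a mean m of 1.40. With inflation 1 + (m − 1)ρ, cancellation needs a within-family correlation ρ of 0.03/0.40 = 0.08 to 0.07/0.40 = 0.18. The document gives neither m nor ρ for this trial.

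**The case against.** The strongest reply is that this rests on silence. The article never says the log-rank test is unstratified, a stratified log-rank test is still a log-rank test, and a fuller protocol or analysis plan could name the strata. That limits the claim to the test as stated. It does not remove the point: the article itself gives the prognostic reason for the strata and then describes a two-group comparison without them, and its 81 per arm matches an unstratified calculation.

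Several stronger readings are tempting but not supported:

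- **Invalid inference.** A reader might infer that the standard errors are wrong in a way that endangers the conclusion. For the strata alone the error is conservative. Siblings act in the opposite direction, so no net direction can be claimed.
- **An underpowered trial.** A loss of 0 to 2 points does not call for a larger N.
- **A known pathway contrast.** The 0.11 is for mood and anxiety disorders in cohort offspring with two or three risk factors, over ages 10 to 20. The 0.29 is for depression alone over one year in another trial's subsyndromal offspring. They are not this trial's two pathways.
- **A biased hazard ratio.** The Statistical analyses section plans a test and names no hazard ratio. A marginal hazard ratio nearer 1 than the conditional one is a different estimand, not an error.

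It is also fair that stratifying has a price: six strata share 21 to 27 events, about 3.5 to 4.5 each. Deciding how to pool after seeing the events would be a data-dependent choice.

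**Conclusion.** The point holds in a limited form. Centre and pathway are built into allocation because they may affect outcome, and the primary test as stated carries neither. Under an assumed 2.6-fold pathway contrast, the strata alone bring one-sided alpha to about 0.043 to 0.048 and cost about 0 to 2 points of power. Losses of 3 to 4 points, 4.6 in one setting, need very strong strata for which the document gives no evidence. These sizes rest on equal-sized strata, three centres, exponential onset and independent children. Shared sibling allocation works the other way by an amount that cannot be computed from the document, so whether the plain test is conservative or liberal overall is open. The planned sample size stands. This is a free improvement of low priority.

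**What to change.** In the Statistical analyses section, state three things:

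1. The primary log-rank test is stratified by each child's own inclusion pathway and by centre.
2. Its variance is family-robust to allow for siblings, for example through the score test of a Cox model stratified in the same way.
3. Sparse strata are pooled by a rule fixed in advance and applied without reference to events by arm. One option is to stratify by pathway only and enter centre as a covariate.

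Centre and pathway are needed for the stratified randomisation, and family membership is needed for the sibling rule, so no new data are required. The cost is a few lines of wording. The simulation shows at most 0.6 point of power lost if the strata turn out not to be prognostic. The sample size is unchanged.

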### Assessments

#### Assessment schedule

Baseline assessment takes place at T0 and comprises questionnaires on the child’s and the parent’s wellbeing (see Table 1). This first screening is used to define the high-risk study population. At T4, all children of parents that were willing to participate will be assessed again with the same measures. The latter is important to evaluate the validity of the initial selection of high risk individuals. If a relatively large proportion of the low-risk group nevertheless has developed a mood or anxiety disorder, this would imply that for future prevention programs the selection strategy should be reconsidered. Selection for the intervention phase is based on the HRI and the RCADS (see Figure 1).

**Table 1 T1:** Assessment schedule for screening (T0) and 24 months follow-up screening

**Measures**	**Child**	**Parent 1**	**Parent 2**
Demographics (+ HRI)		X	
Child anxiety and depression (RCADS)	X	X	
Child impairment (BIS)		X	
Child externalizing symptoms (SNAP)		X	
Parent positive and negative affect (PANAS)		X	X
Optimism (LOT/YLOT)	X	X	X

If a child qualifies for “ultra high risk” based on the screening, he or she may enter the intervention phase of the study. The pre-intervention assessment encompasses structured diagnostic interviews with the child and both parents, as well as a number of relevant other measures (see Table 2). Assessments in the intervention phase are planned for month 0 (T1, at the start of the intervention), month 4 (T2), month 12 (T3), and month 24 (T4). A subset of the instruments is also scheduled for month 6 and 18.

**Table 2 T2:** Assessment schedule for intervention phase

**Measures**	**T1**	**T2**	**T3**	**T4**	**Child**	**Parent1**	**Parent2**
Child diagnoses (DISC)	X	-	X	X	X	X	-
Child anxiety and depression (RCADS)	X	X	X	X	X	X	-
Child impairment (BIS)	X	X	X	X	X	-	-
Child externalizing symptoms (SNAP)	X	X	X	X	X	-	-
Child attachment (IPPA)	X	X	X	X	X	-	-
Implicit child attachment (ABT)	X	-	-	-	-	-	-
Child coping (CSLK)	X	X	X	X	X	-	-
Child attributions (CASQ)	X	X	X	X	X	-	-
Child optimism (YLOT)	X	X	X	X	X	-	-
Child self-esteem (RSES)	X	X	X	X	X	-	-
Expressed emotion (FMSS)	X	-	-	-	-	X	X
Implicit Self-associations (EAST)	X	-	-	-	-	-	-
Child executive functions (BRIEF)	X	-	-	-	-	X	-
Child temperament (EATQ)	X	X	X	X	-	X	-
Parent positive and negative affect (PANAS)	X	X	X	X	-	X	X
Parent depression (BDI)	X	X	X	X	-	X	X
Parent anxiety (BAI)	X	X	X	X	-	X	X

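### The primary log-rank test uses no baseline covariate; pre-specifying adjustment for the baseline RCADS score would give a small, nearly free gain in efficiency

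*Protocol article*

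**What the plan says.** The Statistical analyses section answers the first research question by survival analysis and names one test: "The logrank test (sometimes called the Mantel-Cox test) is a hypothesis test and will be used to compare the" survival distributions of the intervention and control groups over two years. It mentions no covariate or stratum for that test. Explanatory variables appear only in a multilevel model, which the text does not link to the time-to-event comparison. The section neither calls the log-rank test unadjusted nor excludes an adjusted analysis.

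The baseline value is available. Table 2 under Assessment schedule lists "Child anxiety and depression (RCADS") at T1, by child self-report and parent report. The Randomisation section places randomisation after the whole assessment is complete, so the T1 score precedes allocation. The Background names subclinical complaints as a risk factor, without a figure.

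Allocation is stratified by treatment centre and by inclusion pathway (elevated symptoms versus High Risk Index only). Under Participants, the symptom pathway is defined by the 80th percentile of RCADS self-report.

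The Sample size calculation uses "conventional significance (alpha) and power (1-beta) levels of 0.05 and 0.80 respectively, planning one-sided testing". It continues: "We assume a baseline incidence rate of mood and anxiety disorders of 0.11/person*year for the control condition". It assumes a 70% risk reduction and is framed "With an intended follow-up duration of 2 years".

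**The concern.** The trial deliberately mixes symptom-free children with children who already have raised symptoms. If symptom level predicts onset, children within an arm differ in risk, and a test that ignores this gives up some power. With few events, a chance difference in symptom level between arms can also move the result. A pre-specified covariate addresses both at almost no cost, and fixing it in advance prevents a choice of covariates after the data are seen.

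There is a reporting aspect too. The planning is done in hazard ratios, while the only named primary method is a hypothesis test, which yields no effect estimate. A Cox model supplies both.

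**Working it through.** **Inputs from the Sample size calculation.** Control rate 0.11 per person-year; 70% reduction (hazard ratio 0.30; the source trial's unadjusted value is 0.29); 2 years; one-sided 0.05; power 0.80; stated minimum 81 per arm, raised to 102.

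**Step 1: reproduce the sample size.**
- Two-year risks with constant rates: control 1 − exp(−0.22) = 0.1975; intervention at hazard ratio 0.30, 1 − exp(−0.066) = 0.0639.
- Freedman events: (1.645 + 0.842)² × ((1 + HR)/(1 − HR))².
- HR 0.30: 6.18 × (1.30/0.70)² = 21.3 events; 21.3/(0.1975 + 0.0639) = 81.6 per arm.
- HR 0.29: 20.4, rounded up to 21 events; intervention risk 0.0618; 21/(0.1975 + 0.0618) = 81.0 per arm.
- Inflation: 81 × 1.25 = 101.25, so 102.

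The stated 81 and 102 reproduce for a plain log-rank test.

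**Step 2: events and power at the planned size.** 102 × (0.1975 + 0.0639) = 26.7 events with full follow-up. If 20% were lost evenly over two years (an assumption), about 24. Log-rank power at 26.7 events and HR 0.30 is 87% (Freedman) or 93% (Schoenfeld). Simulation gives about 90%.

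**Step 3: what adjustment adds.** The documents give no prognostic strength for RCADS or age, so the values below are assumptions. Each setting has 4,000 simulated trials of 204 children. The log-rank test is compared with a Cox score test adjusted for two standard-normal covariates (symptoms and age). Control two-year risk is held at 0.1975, and the treatment hazard ratio is conditional on the covariates. Monte Carlo error is about 0.5 to 0.8 points for each power. Stratified allocation uses a high/low symptom split.

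| HR | Allocation | Log-HR per SD, symptoms/age | Log-rank | Adjusted |
|---|---|---|---|---|
| 0.30 | simple | 0.3/0.2 | 89.2% | 89.4% |
| 0.30 | simple | 0.5/0.3 | 89.6% | 90.8% |
| 0.30 | simple | 0.7/0.5 | 87.2% | 90.0% |
| 0.30 | stratified | 0.3/0.2 | 89.3% | 89.4% |
| 0.30 | stratified | 0.5/0.3 | 88.8% | 89.8% |
| 0.30 | stratified | 0.7/0.5 | 89.0% | 91.2% |
| 0.50 | simple | 0.7/0.5 | 55.0% | 60.4% |
| 0.50 | stratified | 0.7/0.5 | 55.4% | 59.7% |

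With covariates of no prognostic value, adjustment cost at most 0.4 points (simple allocation, HR 0.30: 90.6% versus 90.2%). Under no effect, rejection rates were 4.1% to 5.4% (log-rank) and 4.1% to 5.6% (adjusted).

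**Step 4: weaker effects.** The Background reports 21% versus 32% onset in the largest comparable trial. At constant hazards that is ln(0.79)/ln(0.68) = 0.61. A second simulation (3,000 runs per setting) used stratified allocation and held the marginal risks at the planned values. For strengths 0.5/0.3 and then 0.7/0.5, log-rank versus adjusted:
- HR 0.30: 90.8% versus 91.5%; 90.3% versus 92.7%.
- HR 0.45: 67.3% versus 70.2%; 68.0% versus 73.4%.
- HR 0.61: 39.8% versus 41.3%; 40.7% versus 44.8%.

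A one-covariate model at 102 per arm and marginal HR 0.45 (2,500 runs; hazard ratio per SD 1.6, 2.0, 2.5) went from 68.8% to 70.5%, 67.6% to 71.0% and 69.1% to 74.0%.

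**The case against.** The strongest case against is that nothing here is wrong. The log-rank test holds its type I error, it matches the sample size calculation, and covariate choice often belongs in an analysis plan that is not shown. At the planned 102 per arm and hazard ratio 0.30 it already exceeds the 80% target. All of that stands, and it limits the point to an improvement. What remains is that the article does fix a test, and a better use of data already collected can be stated in its place.

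Stratification by pathway already limits gross imbalance in symptoms, because pathway is a split of the RCADS itself. That also stands. Calculating chance imbalance as if allocation were simple would overstate the risk. What is left is imbalance in symptom level within a pathway, and the documents do not allow its size to be fixed.

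Symptom-free children enter only with at least two of the three High Risk Index factors, so they carry other risk and the RCADS gradient in this sample may be weaker than expected. This is fair. It points to the lower end of the range.

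A reader might infer lost power from the source trial, where onset in the intervention group is "compared to 0.25 in the control group (unadjusted hazard ratio 0.29") and then "The reported adjusted hazard ratio in this study is 0.18". The documents do not support that. The covariates behind the adjusted value are not given. Hazard ratios are also non-collapsible: a conditional value further from 1 can arise without bias in the unadjusted one and without a matching gain in power.

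A reader might also treat age as an established predictor. The Background says only that depression typically starts 5 to 10 years later than anxiety, which gives no clear direction for a combined endpoint.

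**Conclusion.** The point holds as an efficiency improvement. It is not an error, and the primary test and sample size remain valid without it. Under the assumed prognostic strengths, pre-specified adjustment adds about 0 to 3 points of power at 102 per arm and hazard ratio 0.30, and about 0 to 5 points at hazard ratios of 0.45 to 0.61. Type I error stays near 5%. It also gives some protection, not quantified here, against symptom imbalance within a pathway.

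These figures assume constant event rates, complete two-year follow-up, normally distributed covariates and independent children. Except for the one-covariate results at 0.45, they are for a model with two covariates. The reading that the trial is underpowered for want of adjustment is not supported: simulated log-rank power at the design effect is about 90%.

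**What to change.** In Statistical analyses, define the primary test as the treatment effect in a Cox model with the continuous T1 RCADS self-report score as a pre-specified covariate, at the alpha already planned. Report the hazard ratio with its confidence interval. Keep the log-rank test and Kaplan-Meier curves as the supportive unadjusted result. Age at randomisation may be added, with the note that its prognostic value is only indirectly supported.

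This takes one or two sentences and needs no new data or participants. The costs are that the hazard ratio becomes conditional on the covariates, and that one or two more parameters are fitted to about 27 events.

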For this group of high-risk offspring, we developed an individual cognitive behavioural therapy (CBT) based intervention targeting multiple risk and protective factors known to be associated with the onset of anxiety and depression (as recommended by Cuijpers [24]). Many prevention programs have focused on symptom reduction, whereas training of positive aspects and building resilience may be of utmost importance in prevention. Some at risk children may not show any symptomatology yet, and they may especially benefit from interventions focusing on strengths rather than vulnerabilities. Important protective factors in offspring include having knowledge on parental illness [25], having a supportive social network [22,26] including a non-ill parent if available [27], as well as displaying active coping skills and flexibility in coping style across situations [28]. Therefore, the offspring intervention includes psychoeducation for offspring, psychoeducation for parents, a focus on the social network, and problem solving skills training. With regard to the risk factors, we know that offspring may have a cognitive vulnerability in information processing: they report more negative and less positive self-statements [29]. Interventions focusing on positive self-statements, positive emotions and positive events may enhance resiliency and may function as a buffer against developing negative mood or anxious feelings. A final risk factor are subclinical complaints. These symptoms are addressed by regular behavioural interventions, namely exposure exercises for anxiety and behavioural activation for depressive symptoms. Behavioural activation may be of particular importance, since engaging in activities and relationships outside of the home environment has been found to be an important protective factor in adolescent offspring [25].

So far, most prevention interventions were group-based. Individual programs allow for more tailoring to the specific needs, strengths and weaknesses of the child. This is crucial because of the heterogeneity of the target population (children with anxiety, or depressive symptoms, or no symptoms but an elevated score on the High Risk Index). In addition, living with a depressed suicidal parent differs in many ways from living with anxious dependent one, for example. An individual approach allows the therapist to tailor the intervention also to the specific background of the child.

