#### Intervention

The intervention has 10 child sessions and 2 sessions for the parents. To strengthen the effectiveness of our intervention, it is based on a theoretical framework including both risk and protective factors (as recommended by Cuijpers [24]).The following themes are addressed: family functioning and social network, being proud of strengths, focus on positive emotions and events, problem solving, and breaking the cycle of avoidance behaviour. The latter will either be focussed on behavioural activation (indication for depressive symptoms [35]) or on exposure exercises (indication for anxiety symptoms). The therapist addresses each of the themes in the first sessions and then elaborates on the most appropriate module(s) for each child. In collaboration with the child and the parents, the child chooses 10 steps to work on throughout the sessions. These steps are in line with the aforementioned themes, and could encompass engaging in specific activities, exposure exercises, and exercises on strengths and resilience. Throughout the sessions, the child regularly monitors the frequency and type of activities (categorised as either alone or with others, and either at home or elsewhere). Ideally, children should have satisfying activities in each of these four categories. This registration is available for mediation analyses. The first session is with the parents only. The therapist makes a plan with the parents on how to give age-appropriate information on the parental anxiety or mood disorder to the child in the next session. Parents also receive information on the possible effect on offspring and protective factors against future child psychopathology (such as having a parent or key figure they can trust, and openness in the family). Two more parent sessions further elaborate on positive parenting and defining the social network in terms of social support for the family.

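### The analysis text names siblings as the dependent data but not therapists; if therapist effects are non-zero, a family-only multilevel model would understate the standard error for symptom, quality-of-life and mediator outcomes

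*Protocol article*

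**What the plan says.** The Statistical analyses section assigns the first research question, time to onset of a mood or anxiety disorder, to a logrank test. It then introduces multilevel analysis and gives two reasons for it: the handling of missing data, "as well as the possibility to work with dependent data". For this trial it identifies the dependent units as siblings. It adds that mediators and moderators can enter the multilevel model as explanatory variables. No therapist level is mentioned.

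The Intervention section describes CBT as led by a therapist with considerable discretion: "The therapist addresses each of the themes in the first sessions and then elaborates on the most appropriate module(s) for each child". The Background gives the reason for the individual format: "An individual approach allows the therapist to tailor the intervention also to the specific background of the child". The Secondary outcomes section costs the training of therapists, in the plural. The other arm receives minimal information. The article states neither the number of therapists nor their caseloads.

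**The concern.** With 102 children planned for CBT, it is likely that each therapist treats several of them. Two such children may then have more similar outcomes than two children with different therapists, through skill, adherence or the choice of modules. A minimal-information arm would ordinarily have no matching level, so the clustering would sit in one arm.

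A family random effect does not deal with this. It lets siblings correlate, but it treats children from different families as independent even when they share a therapist. It also concerns only families with more than one child in the trial, whereas therapist clustering concerns every CBT child whose therapist treats another participant. If the correlation is positive and left out, the error goes one way: the variance of the CBT mean is understated, confidence intervals are too narrow, and false positives exceed the nominal level.

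**Working it through.** **The plan's own figure.** The inputs, all from the Sample size calculation section, are:
- "conventional significance (alpha) and power (1-beta) levels of 0.05 and 0.80 respectively, planning one-sided testing";
- a "baseline incidence rate of mood and anxiety disorders of 0.11/person*year for the control condition", so λ1 = 0.11;
- "We assume a risk reduction of 70% for the treatment condition", read as a hazard ratio of 0.30, so λ2 = 0.30 × 0.11 = 0.033;
- "With an intended follow-up duration of 2 years".

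For two exponential rates with censoring at 2 years (Lachin), φ(λ) = λ²/(1 − exp(−2λ)) and

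n per arm = [1.645 √(2φ(λ̄)) + 0.842 √(φ(λ1) + φ(λ2))]² / (λ1 − λ2)²,

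with λ̄ = (0.11 + 0.033)/2 = 0.0715. Here φ(0.11) = 0.0613, φ(0.033) = 0.0171 and φ(0.0715) = 0.0384. The result is n = 80.6, which rounds up to the stated "minimum of 81 participants per condition". Then 81 × 1.25 = 101.25, which gives 102 per arm. The figure reproduces with independent children and no design effect of any kind.

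**Effect of leaving therapists out.** Let K be the number of therapists, m = 102/K the caseload and ICC the therapist intraclass correlation. Both K and ICC are assumptions. I also assume equal caseloads, equal outcome variance in the two arms and 102 children per arm, and I set sibling correlation aside.

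- CBT-arm variance inflation: DE = 1 + (m − 1) × ICC. The control arm has 1.
- True SE / naive SE of the arm difference: √((1 + DE)/2).
- Actual one-sided error at nominal 5%: 1 − Φ(1.645 / ratio).

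| K | m | ICC | DE | SE ratio | Actual one-sided error |
|---|---|---|---|---|---|
| any | – | 0 | 1.00 | 1.00 | 5.0% |
| 30 | 3.4 | 0.02 | 1.05 | 1.01 | 5.2% |
| 30 | 3.4 | 0.05 | 1.12 | 1.03 | 5.5% |
| 10 | 10.2 | 0.02 | 1.18 | 1.05 | 5.8% |
| 10 | 10.2 | 0.05 | 1.46 | 1.11 | 6.9% |
| 6 | 17 | 0.02 | 1.32 | 1.08 | 6.3% |
| 6 | 17 | 0.05 | 1.80 | 1.18 | 8.2% |

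Worked line for K = 6, ICC = 0.05: DE = 1 + 16 × 0.05 = 1.80; ratio = √(2.80/2) = 1.183; 1.645/1.183 = 1.390; upper tail 8.2%. At ICC 0.10, outside the range I rely on, the ratio runs from 1.06 (30 therapists) to 1.34 (6 therapists).

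The formula is for a difference in means, so it suits the symptom and quality-of-life scores. The article states its 5% one-sided level for the sample size of the time-to-onset comparison; I use that level here only as a yardstick.

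**Events available for time to onset.** Under the plan's own rates, expected CBT events are 102 × (1 − exp(−2 × 0.033)) = 102 × 0.0639 ≈ 6.5. That is too few to estimate a therapist-clustered variance reliably.

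**The case against.** The best reply is that the article is a condensed account. It cites siblings as its case of dependent data but does not say that they are the only level, and a full list of random effects commonly sits in the full protocol or analysis plan. That stands as far as it goes: a reader might infer that siblings are the only dependence to be modelled, and the text does not say so. What remains is that the section does take up dependence for this particular trial and names one source. An analyst who builds the model from that text would leave therapists out.

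Second, the premises are partly inferred. No caseload is given, the delivery of the minimal-information arm is not described, and freedom to tailor treatment does not by itself prove correlation within therapist. A reader might conclude that the standard errors will be too small. The documents do not support that certainty: at ICC 0 nothing changes, and with 30 therapists and ICC 0.02 to 0.05 the understatement is only 1 to 3%.

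Third, a reader might carry the criticism over to the primary result. The stated primary test is a logrank test, not the multilevel model, and the calculation above does not quantify a therapist effect on it. Nor do the documents support saying that the findings would apply only to these particular therapists.

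**Conclusion.** The point holds in conditional form. The design is probably partially nested, and the article's account of dependence does not mention the therapist level. If therapist effects are non-zero, a family-only multilevel model understates the standard error for symptom, quality-of-life and mediator outcomes. The size ranges from nil to 18% on the standard error, and from 5.0 to 8.2% for a nominal one-sided 5%, over 6 to 30 therapists and ICC 0 to 0.05. It becomes material only with few therapists and a non-trivial ICC. Therapist number, ICC and equal caseloads are all assumptions. Nothing here shows that the sample size was miscalculated or that the primary logrank comparison is invalid.

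**What to change.** - State the number of therapists and record the treating therapist for each CBT child. Therapist time is already monitored for costing, but the article does not say that identity is kept per child, so this must be confirmed.
- In the multilevel models, add a therapist random effect that applies to the CBT arm only, next to the family effect. Treat the two as crossed if siblings may have different therapists; the article does not say that siblings share one.
- Use a small-sample correction to the degrees of freedom, because therapists may be few.
- For time to onset, report therapist clustering only as an exploratory sensitivity check, given the 6 to 7 CBT events expected.

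The cost is analysis wording and one recorded variable, with no change to recruitment, allocation or treatment. Confidence intervals become slightly wider, and the therapist variance may be estimated imprecisely. If it is close to zero, the results will barely move.
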